### Interventions

All participants can only receive the assigned treatment and a standard education.

booklet during the course of the study. They will be asked not to use any analgesics during the trial unless strictly necessary. All medication intake will be reported, and exclusion will be considered if a drug is taken for more than three days after enrolment. The participants will be asked to report any adverse event during the treatment period.

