**Methods:**

We will conduct a prospective randomised controlled trial including 150 patients with WRNP. These patients will be randomly assigned to one of three groups: (i) home exercise (TE), (ii) home exercise plus Occiflex therapy and (iii) home exercise plus manual therapy delivered by a physical therapist. Ten treatment sessions will be performed in four weeks. During the trial, these patients will receive only the assigned treatment and the standard patient education and will be asked not to use any analgesics unless strictly necessary. Assessments by trained evaluators will occur at baseline, week 4 and week 12. The primary outcome measures will include visual analogue scale (VAS) for pain and neck disability index (NDI) at each time point. Secondary outcome measures will include cervical range of motion (CROM), pressure pain threshold (PPT), global perceived effect (GPE) and sick leave. Group by time differences will be analysed using linear mixed models with repeated measures.

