#### Group b (Occiflex group): Occiflex + Home exercise + Booklet education

Patients in the Occiflex group will receive the standard home exercise programme and health education as group A combined with the computerised mobilisation (Occiflex) treatment. The Occiflex device can record any head and neck mobilisation in a 3D space as performed by the physiotherapist (Fig. 3a). The recorded mobilisation will be used as a template for repeated movement (Fig. 3b). The participants allocated to the Occiflex group will be divided into three categories according to their symptoms and a physical examination of their neck pain [7]: (a) neck pain with mobility deficits; (b) neck pain with headache (cervicogenic); and (c) neck pain with shoulder radiating pain (radicular). Individualised mobilisation will be determined for each category following three principles [18]: (a) stretching shortened or tight muscles; (b) mobilisation of facet joints relevant to pain; and (c) extending the limited range of motion based on the CROM examination. This mobilisation programme will be determined by an experienced physiotherapist during the first visit and performed using a computer afterwards. Each treatment session will last for 20 min and will be done every 3 days for a total of 10 times in 1 month.

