#### Group c (Manual group): Manual therapy + Home exercise + Booklet education

The participants in the manual group will receive the standard home exercise programme and health education combined with manual therapy based on the neck pain clinical practice guidelines. Similar to Group B, all participants in this group will be divided into three categories and treated with cervical and thoracic mobilisation accordingly [7]. The physiotherapist who performs manual therapy must be qualified and should have received the standardised training as described in *Maitland’s Vertebral Manipulation (7th edition)*. Each treatment will last for approximately 20 min and will be performed every 3 days for 10 times in 1 month. The manual therapy technique [21–23], which consists of three parts, is illustrated in Fig. 4.

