### Outcome measures

Personal information, including age, gender, BMI, international physical activity questionnaire (IPAQ) [24], working years and time since the onset of symptoms, will be collected at the baseline. The primary outcome measurements will include the VAS for pain and NDI to be administered at weeks 4 and 12. Secondary outcomes will include CROM, pressure pain threshold (PPT), global perceived effect (GPE) and sick leave. These evaluations will be carried out by an evaluator trained with these procedures. The adverse reactions during therapy will also be recorded.

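### Adverse events are requested only during the roughly four-week treatment period, so none starting in the remaining eight weeks to the week-12 assessment is actively solicited in any arm

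*Protocol article*

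**What the plan says.** Safety collection is described in two sentences of the protocol article. Under Interventions: "The participants will be asked to report any adverse event during the treatment period". Under Outcome measures: "The adverse reactions during therapy will also be recorded". Both attach the collection to treatment.

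The treatment period is about four weeks. The abstract's Methods paragraph states that "Ten treatment sessions will be performed in four weeks". For the Occiflex arm, "Each treatment session will last for 20 min and will be done every 3 days for a total of 10 times in 1 month"; for the manual arm, treatment "will be performed every 3 days for 10 times in 1 month". The home exercise programme, common to all arms, also runs four weeks.

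Outcome follow-up is longer: "Assessments by trained evaluators will occur at baseline, week 4 and week 12". The VAS section treats week 12 as part of the study period and labels it the three-month follow-up.

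On analgesics, Interventions says: "They will be asked not to use any analgesics during the trial unless strictly necessary". The same section limits participants to their assigned treatment and the education booklet for the course of the study.

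**The concern.** The trial intends to report benefit at week 12, but the harms it asks about end with treatment at about week 4. A symptom that begins days after the last mobilisation, or at any time in weeks 5 to 12, is not the subject of any described question.

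This matters somewhat more here than in many exercise trials, because safety is part of the case for the device. The Background section cites mild to moderate adverse effects of upper-spine manipulation and presents computerised mobilisation as a way round the safety issues of manual therapy. A comparison of harms between the Occiflex and manual arms is therefore of direct interest. As written, that comparison stops at week 4, and what is known after it depends on unsolicited reports. The trial is open-label, so such reports may be incomplete and may differ between arms for reasons unrelated to the treatments.

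**Working it through.** **Inputs**
- Sessions: 10, every 3 days, in four weeks or one month (abstract, Methods; Group b; Group c).
- Home exercise: four weeks (Group a).
- Last assessment: week 12 (abstract, Methods; VAS section).
- Planned sample size: 150; expected dropout: 20% (Sample size calculation).

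**Step 1: reproduce the four-week treatment period.** If session 1 is on day 1, session k is on day 1 + 3 × (k − 1). Session 10 is on day 1 + 3 × 9 = 28. The stated four weeks is reproduced.

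**Step 2: time left in the window after the last session.** With a 28-day window: 28 − 28 = 0 days. If one month is taken as 30 days: 30 − 28 = 2 days. This assumes a day-1 start and exact 3-day spacing, so it is indicative only.

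**Step 3: share of each participant's follow-up without solicitation.** (12 − 4) / 12 = 8/12 = 67%. The window covers 4/12 = 33%.

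**Step 4: person-weeks over the whole trial.**

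| Assumption | Covered | Not covered | Total |
|---|---|---|---|
| No dropout | 150 × 4 = 600 | 150 × 8 = 1,200 | 1,800 |
| All 20% dropout leaves at week 4 | 150 × 4 = 600 | 120 × 8 = 960 | 1,560 |

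The second row uses 150 × 0.8 = 120 participants after week 4. The uncovered share is then 960 / 1,560 = 62%.

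**Step 5: what other data cover weeks 5 to 12.**
- VAS, NDI, CROM, PPT and GPE at week 12 show a state or a perceived change at one time point. They give no event, onset date or cause.
- Sick leave is asked from the last treatment onward, with length and frequency, but only absence due to neck pain is counted.
- Medication intake is to be reported. Whether this reaches week 12 depends on how the undefined wording in Interventions is read.

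A flare-up of neck pain could leave a trace in these data. A new symptom of another kind, such as a headache or a neurological complaint, could be missed. In neither case is event type, onset or relation to treatment recorded.

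**The case against.** The strongest reply is that the window is a disclosed and consistent choice. Both sentences agree, and limiting safety reports to the exposure period of a four-week physical therapy is understandable. It does not touch the primary outcomes, their analysis or the power. The documents give no rate of delayed harm, and harm related to exposure need not spread evenly over the eight weeks after exposure ends. All of this stands, and it keeps the point minor.

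A second reply is that an article condenses the full protocol, where serious-event follow-up and the detailed reporting window may be set out. This stands in part: one cannot conclude that later events would go unhandled. But the article does not leave the window unsaid; it states the same limit in two places.

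Three stronger readings are tempting, and the documents do not support them:
- *Later events are excluded by rule.* Neither sentence bars or discards a later report. The text supports only that none is requested.
- *Nothing about harm is collected after week 4.* The data in step 5 of the working would partly show worsening, so it is also too absolute to say that a poor week-12 score could never be linked to an earlier event.
- *Participants remain under trial restrictions to week 12 with no safety collection.* The terms used for the analgesic request and the assigned-treatment limit are undefined. The VAS section supports a 12-week reading, but the abstract mentions the restrictions directly after the four weeks of sessions, and no section expressly extends them to week 12.

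**Conclusion.** The point holds in its limited form and is of minor severity. As the article is written, no adverse event starting after the last sessions is actively solicited in any arm, although outcomes are assessed eight weeks longer. The gap is about two thirds of planned follow-up time (62% under the dropout assumption in the working). The figures assume that the window closes at four weeks and, for the first, that nobody drops out; they make no statement about how many events would be missed. The conclusion does not depend on how long the analgesic and treatment restrictions last.

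**What to change.** Amend the two sentences in Interventions and Outcome measures so that adverse events are collected from randomisation to the week-12 assessment in all three arms. At the existing week-4 assessment ask about events to date, and at the existing week-12 assessment ask about events since week 4. Use the same question in every arm and record the onset date. Tabulate events on treatment and events in follow-up separately by arm.

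The cost is a short protocol amendment and one question at each of two assessments already planned; no visit is added. The downside is slightly longer forms and the recording of some events unrelated to treatment.

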#### Group a (HE group): Home exercise + Booklet education

The participants in the HE group will be instructed to carry out a standardised home exercise programme regularly five times a week for four weeks on their own. The protocol will be taught to these participants during the first week and will be reinforced by a physiotherapist during their visit to the department. The actual amount of time will be recorded in a training diary and checked at each visit. Those participants who perform the home exercises less than three times a week will be withdrawn from this study. All participants will also receive booklet education on different topics, including office ergonomics and recommended neck exercises. The exercise prescriptions are listed in Table 2  [5, 21]. Figure 2 shows the standard home exercise programme using Thera-band in different positions.

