### Randomisation

After completing the baseline assessment, the eligible subjects will be randomised in equal portions to the home exercise group, Occiflex group and manual therapy group via a computer-generated block allocation with a block size of 6 or 9. Randomisation will be stratified by the baseline score (≤ 25 vs. ≥26 on a 0–50 scale) on the neck disability index (NDI) and balanced by gender in a 2: 1 ratio (female vs. male) for each group. This procedure ensures that the participants with the same severity of neck disability will be allocated to each group and that all groups are comparable in sex. Both the entry process and group allocation are unblinded to the researchers, examiners and participants.

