### Statistical analysis

The statistical analysis will be carried out using the IBM SPSS Statistics 26 software. Descriptive statistics will be used to describe the study population and will be summarised per group based on the number of observations, means and standard deviations. The primary and secondary outcome variables (VAS, NDI, CROM, PPT and GPE) will be analysed by intention to treat and by using linear mixed models with repeated measures. The linear mixed model requires the residuals to be normally distributed. The Shapiro–Wilk test will be applied to test the normality. In case of a non-normal distribution of the residuals, an appropriate non-parametric test will be conducted. Multiple post-hoc comparisons will be conducted through Bonferroni’s contrast for parametric distributions. All tests will be two sided, and the level of significance is set to 0.05. The missing data in this study will be handled with a mean imputation or mixed modelling approach.

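### Withdrawal for low exercise adherence, and possible exclusion for drug use, act after randomisation, conflict with the stated intention-to-treat analysis and can bias the comparison of arms

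*Protocol article*

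**What the plan says.** All of this comes from the protocol article.

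- Randomisation section, on timing: "After completing the baseline assessment, the eligible subjects will be randomised in equal portions to the home exercise group, Occiflex group and manual therapy group". The same section says that allocation is known to researchers, examiners and participants.
- Group a (HE group): "Those participants who perform the home exercises less than three times a week will be withdrawn from this study". The exercise programme runs for four weeks, and training diaries are checked at each visit. Groups b and c follow the same home programme, but their sections do not repeat this rule.
- Interventions, on analgesics: "They will be asked not to use any analgesics during the trial unless strictly necessary". On medication in general: "exclusion will be considered if a drug is taken for more than three days after enrolment".
- Statistical analysis: the outcomes "will be analysed by intention to treat and by using linear mixed models with repeated measures". On gaps in the data: "The missing data in this study will be handled with a mean imputation or mixed modelling approach".
- Outcome measures: VAS and NDI, the primary outcomes, are taken at baseline, week 4 and week 12.

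**The concern.** An intention-to-treat analysis compares everyone randomised, in the arm to which they were assigned. Here one rule takes participants out of the study, not merely off treatment, for behaviour after assignment. A second rule allows staff who know the arm to do the same at their discretion. Both triggers may be related to outcome. Analgesics are to be used only when strictly needed, so several days of use may track pain, which is a primary outcome. Low exercise adherence may reflect burden, lack of benefit, lack of time or early improvement.

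If such people leave in different proportions, or for different reasons, in the three arms, the groups that remain are no longer the groups that were randomised. This touches both primary outcomes and every between-arm contrast. If outcomes are not collected after withdrawal, no later analysis can recover them.

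**Working it through.** **Step 1. Timing.** Randomisation follows the baseline assessment. The adherence rule operates during the exercise programme, and the drug rule operates after enrolment. Adherence can be judged only once the programme has started, so that rule acts on people already randomised. The drug rule, counted from enrolment, also reaches them.

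**Step 2. The rules beside the analysis statement.** The adherence rule is definite and concerns leaving the study. The drug rule is conditional. The analysis is by intention to treat. The article does not say whether those withdrawn or excluded are still assessed at weeks 4 and 12, or how they enter the analysis. The stated rule and the stated analysis population therefore conflict.

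**Step 3. Does the missing-data text resolve it?** The first post-baseline assessment is at week 4. A participant withdrawn before then, and not followed further, has only a baseline VAS and NDI.
- *Mixed model:* it keeps that value, but it is valid only if observed data explain who is missing.
- *Mean imputation:* suppose 20% of an arm is missing and the mean of those kept is m. Filling in m gives 0.80 × m + 0.20 × m = m. Any shift caused by the removal stays in full. (The article does not say which mean would be used; this takes the arm's own observed mean.)

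**Step 4. Illustrative size, simple form.** The plan gives no removal rates, so these inputs are assumptions. Let w be the share removed and g the gap in NDI between those removed and those kept. The full-arm mean is (1 − w) × m + w × (m + g) = m + w × g, so the shift is w × g.
- w = 0.20, g = 5: 0.20 × 5 = 1.0 point.
- w = 0.30, g = 5: 0.30 × 5 = 1.5 points.
- w = 0.20, g = 2.5: 0.20 × 2.5 = 0.5 point.

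Between two arms, the net bias is w₁g₁ − w₂g₂. It is zero when rates and gaps are equal.

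**Step 5. Illustrative size, range over differential removal.** Assume no true effect, an NDI standard deviation of 8 (from Sample size calculation), normal distributions, a correlation ρ between adherence and outcome, and removal of the lowest adherers. The shift in an arm is ρ × 8 × φ(z_w) / (1 − w), where z_w is the normal quantile at w and φ is the normal density. For w = 0.30 and ρ = 0.5: φ(z_w) = 0.348, and 0.5 × 8 × 0.348 / 0.70 = 1.99. The differences between two arms, in NDI points, are:

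| Removed, arm 1 vs arm 2 | ρ = 0.1 | ρ = 0.3 | ρ = 0.5 |
|---|---|---|---|
| 10% vs 10% | 0 | 0 | 0 |
| 20% vs 10% | 0.12 | 0.37 | 0.62 |
| 30% vs 10% | 0.24 | 0.72 | 1.21 |
| 20% vs 0% | 0.28 | 0.84 | 1.40 |
| 30% vs 0% | 0.40 | 1.19 | 1.99 |

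The yardstick is the plan's own clinically important NDI difference of 5 points.

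**Step 6. Direction.** It depends on who is removed. If those removed from the home-exercise arm would have done worse, that arm looks better than it is and the benefit of adding mobilisation is understated. If they had stopped exercising because they felt better, the reverse holds.

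**The case against.** Several points on the other side are fair.

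- **Certainty of removal.** A reader might infer that people will be removed for taking analgesics. The text does not go that far: exclusion is only to be considered, and the trigger is a drug, not analgesics specifically. Only the adherence rule is definite.
- **No outcome data.** A reader might infer that anyone withdrawn has no week 4 or week 12 data. The article does not say that outcome collection stops, and someone excluded after week 4 would already have that assessment. Follow-up after withdrawal and analysis sets are also details that a journal article commonly leaves to the full protocol or SAP, so their absence is not the point here. The point is that the stated withdrawal rule and the stated analysis conflict.
- **The mixed model.** Nothing in the article specifies deletion of incomplete cases. A repeated-measures mixed model keeps what was observed and is valid when observed data explain the missingness. This stands, but it does not cover removal that depends on unobserved outcomes, and mean imputation is offered as an alternative.
- **Scope of the adherence rule.** It stands in the only section that describes the exercise programme, and the other arms adopt that programme. It may be meant for all three arms. So its placement is an ambiguity to settle, not proof of different handling.
- **Dropout allowance.** The 20% in Sample size calculation may already include rule-driven withdrawals.

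These points narrow the concern. They do not reconcile withdrawal from the study with intention to treat.

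**Conclusion.** The conflict is established from the text: one mandatory and one discretionary rule act on randomised participants, and the analysis is described as intention to treat. The bias is a possibility. It requires that removal differs between arms, in rate or in its relation to outcome, and that the analysis does not account for this.

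The illustrations give 0 with equal removal and equal outcome relations, 0.12 to 1.99 NDI points over the unequal scenarios in the table, and 1.0 to 1.5 points for 20% to 30% removed from one arm with a 5-point gap. All rest on assumed removal rates and assumed relations to outcome. A reader might infer that poor outcomes will be lost mainly from the less effective arm; the documents do not support that, and neither size nor direction can be known from them. The point should still be settled now, because outcomes that are not collected cannot be restored at analysis.

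**What to change.** Reconcile the Interventions and Group a sections with the Statistical analysis section by stating that:

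1. low exercise adherence or medication use does not end outcome follow-up;
2. all randomised participants are assessed at weeks 4 and 12 and analysed in the arm to which they were randomised;
3. adherence and medication use are recorded, and any criteria based on them define only a supplementary per-protocol or sensitivity analysis, applied identically in all three arms.

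How low adherence or medication use is managed clinically is left to the investigators; nothing here proposes a rule on either.

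The cost is a short amendment and some extra follow-up of people who might otherwise have left. The estimate will include non-adherers, so it may be smaller than one restricted to those who complied.

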**Fig. 2 Fig2:**
[figure not shown]
Standard therapeutic exercise program. **a** Cranio-cervical flexion in supine position; (**b**) Cranio-cervical flexion in Quadrupedal position; (**c**) neck movement and cranio-cervical flexion in sitting position; (**d**) Co-contraction deep and superficial neck flexors with Thera-band; (**e**) exercise for lower trapezius and scapular muscles with Thera-band; (**f**) Resisted shoulder elevation with Thera-band

**Table 2 Tab2:** List of exercises and prescriptions in the standard home exercise program

Exercise	Position	Description
1	Supine	Cranio-cervical flexion (CCF) with a towel on the back of neck for 10s, 10 repetitions with 10s rest, 3 sets totally (Fig. 2a)
2	Quadrupedal	Neck in neutral position, perform the cranio-cervical flexion and maintain the posture for 10s, 10 repetitions with 10s rest, 3 sets (Fig. 2b)
3	Sitting	Move neck into flexion, extension, side flexion and rotation to each side. Then perform cranio-cervical flexion for 10 repetitions and each with 10s of contraction (Fig. 2c)
4	Sitting	Co-contraction deep and superficial neck flexors with Thera-band for 10 repetitions, 3 sets totally (Fig. 2d)
5	Sitting	Co-contraction exercise for lower trapezius and scapular muscles with Thera-band for 10 repetitions, 3 sets totally (Fig. 2e)
6	Standing	Resisted shoulder elevation exercise in scapular plane with Thera-band (Fig. 2f)

Notes: Participants will be given the exercise instructions within different sessions (Session 1-2: Exercise 1 and 2; Session 3-6. Exercise 1, 2, 3 and 4; Session 7-10. Exercise 1, 2, 3, 4, 5 and 6). Each session of exercises should not last more than 30 minutes to avoid fatigue

